### Statistical analysis

All analyses will be conducted on a modified intention-to-treat (ITT) population, comprising all randomized participants with a completed baseline and at least one completed valid post-baseline assessment.

The study will incorporate the use of generalized estimating equations (GEE) as the regression model to analyze the changes in study outcomes (social media use and its attributable child-family relationship, alcohol consumption, as well as sexual health issues) over the specified periods. The formal mathematical framework and specification of the GEE model equations are provided in S6 File. This comprehensive approach will provide more accurate and reliable insights into the effectiveness of the intervention across different socio-demographic variables, economic variables, and time intervals in the data.

The GEE model shall be adjusted for different socio-demographic and economic variables as well. GEE is applicable for both continuous and categorical study outcomes, and in the present study, the outcomes are both metric and categorical. For categorical outcomes, the GEE procedure can be executed with the maximum likelihood estimation (MLE) algorithm described

Additionally, a repeated measures analysis of ANOVA shall be used to study the effectiveness of the intervention across different periods of intervention. The statistical analysis shall be carried out using Stata version 17. The results will be considered statistically significant if the P-value is less than 0.05.

Further, the qualitative assessment of the exit interviews to elicit feedback and identify general challenges/barriers in executing the intervention will be analysed using thematic analysis and transcript interpretation by employing open-source MAXQDA software.

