### Study area and settings

The study will be conducted in senior secondary schools located in three cities in Northern India (Chandigarh, Panchkula, and Mohali). A total of 12 schools will be selected, comprising four schools from each study area. Within each city, schools (clusters) will be randomized into intervention and control arms (Fig 2). The protocol paper has been prepared following SPIRIT 2025 guidelines (S1 File).

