### Phase 2: The Intervention Phase

#### Sample size for the intervention phase.

For Phase 2, based on the available literature on sample size guidelines for Randomized Controlled Trials. [17], for a 95% confidence level for the two-tailed hypothesis (${\text{Z}}_{\alpha }$= 1.96) and to achieve a power of 90% (${\text{Z}}_{\text{1}-\beta }$ = 1.2816), with an assumed standard deviation of population 0.15 and estimated effect size (D) of 5%, a minimum sample size of 189 per arm/group is required for the study, as per the following for the cluster-level randomization:

$$\begin{array}{c} \text{n}=\frac{{\;\text{2}\left({\text{Z}}_{\alpha }+{\text{Z}}_{\text{1}-\beta }\right)}^{\text{2}}\sigma^{\text{2}}}{(D{)}^{\text{2}}} \end{array}$$

By considering an attrition rate (10%), the sample size for each group (control and intervention) has come out to be approximately 208 participants in each of the control and intervention groups. Therefore, the minimum sample size for both control and intervention groups comes out to be 416 per study location. The total sample size is estimated to be n is equal to 1248, including all three cities in Northern India. To align with the baseline sample size, the RCT will also include 1,260 participants across all three cities.

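### The repeated-measures ANOVA, planned as an additional test of effectiveness, has no school level although schools are randomised; its arm test would have a true error of about 11% to 43% at assumed ICCs of 0.005 to 0.05

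*Protocol article*

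**What the plan says.** On the unit of randomisation, the Protocol article is clear (Study area and settings): "Within each city, schools (clusters) will be randomized into intervention and control arms". The section on the sampling strategy for the trial gives 6 intervention and 6 control schools, and the baseline sampling section gives 105 students per school. Phase 3 sets five assessments, T0 to T4.

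The Statistical analysis section plans "generalized estimating equations (GEE) as the regression model to analyze the changes in study outcomes" and refers the model equations to S6 File. It then adds a second analysis: "a repeated measures analysis of ANOVA shall be used to study the effectiveness of the intervention across different periods of intervention". One threshold covers everything: "The results will be considered statistically significant if the P-value is less than 0.05". The section does not mention school, cluster, ICC, robust variance or a correction for few clusters. Only the GEE equations are referred to S6; the ANOVA is referred to no other file.

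**The concern.** A repeated-measures ANOVA has a student level and a time level. Without a school term, its error for the arm comparison is the variation between students. When whole schools are allocated, the arm difference also carries the variation between schools, and there are only six per arm. Leaving that out makes standard errors too small, P-values too low and confidence intervals too narrow.

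The ANOVA is prescribed, not merely mentioned as an option, and it is described as a test of effectiveness. A significant result from it could therefore be reported as evidence that the programme works. The economic evaluation looks ahead to routine use in a national programme, so a false positive would matter beyond this trial.

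**Working it through.** **1. The plan's own figure.** The section on sample size for the intervention phase uses a "95% confidence level for the two-tailed hypothesis" (z = 1.96), 90% power (z = 1.2816), an "assumed standard deviation of population 0.15" and D = 0.05:

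n = 2(1.96 + 1.2816)² × 0.15² / 0.05² = 2 × 10.508 × 9 = 189.1 per arm per city.

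Then 189 × 1.10 = 208; 208 × 2 = 416 per city; 416 × 3 = 1,248, raised to 1,260. The figure reproduces. The formula is labelled as one for cluster-level randomisation, but it is the formula for two independent means and has no ICC term. The article therefore supplies no ICC, and the values below are assumptions.

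**2. Arm effect in a test that ignores school.** With m = 1,260 / 12 = 105 students per school:

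- design effect DE = 1 + (m − 1) × ICC
- true two-sided error = 2[1 − Φ(1.96 / √DE)]

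| ICC (assumed) | DE | 1.96/√DE | True error | 1,260 / DE |
|---|---|---|---|---|
| 0.005 | 1.52 | 1.59 | 11% | 829 |
| 0.01 | 2.04 | 1.37 | 17% | 618 |
| 0.02 | 3.08 | 1.12 | 26% | 409 |
| 0.03 | 4.12 | 0.97 | 33% | 306 |
| 0.05 | 6.20 | 0.79 | 43% | 203 |

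With 10% attrition (m = 94.5) the errors at ICC 0.005, 0.01, 0.02 and 0.05 are 11%, 16%, 25% and 41%, so the result hardly depends on m.

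Simulation under no effect (12 schools, assumed 2 v 2 in each city, 105 students, 5 times, within-student variance share 0.5, 1,500 runs per setting) gave 21%, 34% and 49% for the between-arm ANOVA test at ICC 0.01, 0.02 and 0.05. These exceed the formula because averaging over visits removes within-student noise but not the school effect.

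**3. Arm-by-time test.** In the same simulation:

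- school effect constant over time: 4% to 7%, that is, about nominal;
- school-by-time variance share of 0.005, 0.01 and 0.02: 33%, 56% to 59%, and 77%.

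A second simulation (95 students per school, cluster autocorrelation 0.8, student correlation 0.6) gave 18%, 31%, 42% and 58% at ICC 0.01, 0.02, 0.03 and 0.05. The size depends strongly on the assumed school-by-time variation; without such variation there is no inflation.

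**4. The GEE, under specifications that S6 might contain.**

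- *School as cluster, uncorrected sandwich, normal reference.* Without covariates in a balanced 6 v 6 layout, the sandwich averages 5/6 of the unbiased variance, so the error is P(|t₁₀| > 1.96√(5/6)) = 0.104, or 0.091 with a 12/11 factor. With city terms it is P(|t₈| > 1.96√(8/12)) = 0.148, or 0.133 with the factor. Simulation with 40,000 runs agrees: 0.106 and 0.093 without city, 0.150 and 0.134 with city.
- *Student as cluster, arm effect on change.* About 5% with a constant school effect, and 17% to 39% with the school-by-time variance shares in step 3.
- *School as cluster, bias-corrected sandwich, t reference.* 2% to 4%.

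**5. Benchmark.** A t test on 12 school summaries (10 df) held about 5% (4.5% to 6.5% across settings).

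**The case against.** The strongest reply is that the GEE is the named regression model, the ANOVA is only an addition, and the GEE specification sits in a file that is not shown. That stands as far as the GEE is concerned. A reader might infer that every planned test will exceed 5%, but the documents do not support this: S6 may cluster on school and correct for 12 clusters, and the P<0.05 threshold is compatible with such a correction. The reply does not rescue the ANOVA, which is prescribed in the article and not referred to S6.

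A second reply is that a test of effectiveness across periods most naturally means arm by time, where a school effect that is constant over time cancels. That is right, and it makes the arm-by-time inflation conditional. The wording does not confine the ANOVA to that term, and nothing in the plan assures that schools will move in parallel over the follow-up.

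Three further inferences are tempting and should not be drawn:

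- *A third of students would be lost.* Complete-case ANOVA would lose 1 − 0.9⁴ = 34% if 10% were missing independently at each of four visits. The article states 10% attrition once, and its modified intention-to-treat set requires only one valid post-baseline assessment. How the ANOVA would treat incomplete students is not stated.
- *The ANOVA will be applied to categorical outcomes.* The article says that the GEE handles both outcome types. It does not say this of the ANOVA.
- *There is no order between the two tests.* The ANOVA is introduced as an addition, so an order is implied. A formal hierarchy may stand in an analysis plan that is not shown.

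**Conclusion.** The point holds for the ANOVA. As written, it is an effectiveness test at P<0.05 that leaves out the level at which treatment is allocated. The error of 11% to 43% for the arm effect rests on assumed ICCs of 0.005 to 0.05, about 105 students per school, and an analysis with no school term. Inflation of the arm-by-time test rests on the further assumption that schools differ in their change over time.

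For the GEE there is only a matter to confirm. The 9% to 15% applies if S6 uses school clusters with an uncorrected sandwich and a normal reference, and the documents do not show whether it does.

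**What to change.** - Delete the repeated-measures ANOVA as a test of effectiveness.
- Take the period-specific effects (T1 to T4) from the arm-by-time contrasts of the one GEE.
- State in the article, or confirm that S6 states, that school is the GEE cluster, that city is a fixed effect because schools are randomised within it, and that a small-sample corrected variance is used with a t reference suited to 12 clusters. With an intercept, arm and two city terms, 12 − 4 = 8 degrees of freedom is a natural choice. Which correction to use is for the trial team, provided it is fixed before the data are analysed. If S6 already specifies all this, only the ANOVA sentence changes.

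The cost is a few lines of wording and code, and wider confidence intervals. Relative to an analysis that ignores school, the standard error of the arm effect grows by about √DE (1.43 at ICC 0.01, 2.49 at ICC 0.05). The t reference on 8 df adds a further factor of 2.306 / 1.96 = 1.18. That width reflects what 12 randomised schools can show. Data collection is planned to run to 30/06/2027, so the change can be made before results are available.

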### Phase 3: Post-intervention phase

Assessments of outcomes will be conducted after completing the three-month intervention phase and for three months following the intervention closure. The Social Media Use Scale (SMUS), Family Relationship Scales, Family Leisure Activity Profile, WHO’s Alcohol Use Disorders Identification Test (AUDIT), and Sexual Health Practice Tool tools will be administered at baseline (T0) and at four time points after implementation of the intervention. The time points will include immediately post-intervention (T1) and at one-month post-intervention (T2), two months post-intervention (T3), and three months post-intervention (T4) for both the intervention and control groups. After three months of active intervention, the follow-up period will be passive. During the three-month follow-up, the intervention maintenance phase will be implemented. Additionally, the utilization of the Readiness to Behaviour Change Questionnaire is planned to assess the stage of behavioural change of students.

Exit interviews (approximately 50 interviews) will be conducted to elicit feedback and identify general challenges/barriers in executing the intervention from parents, teachers, and students as part of the research process

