## Results chain of the study

This study protocol introduces a new approach to aware the adolescents about the harmful effects of excessive social media use. As shown in Fig 5, the inputs to the study will be extramural grant funds, staff for implementation of the study, schools, and validated tools. The program activities include designing the intervention, delivering the intervention, and assessing the change in behaviour at different intervals. The outputs will be newly developed IEC tools, teachers trained through sensitization workshops, and adolescents recruited in the intervention group. The outcomes consist of reduction in time spent on social media, reduction in risky sexual behaviour, enhanced awareness regarding the risks of alcohol use, and reduced conflict within child-family relationships.

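### One unadjusted P<0.05 rule covers every result, while the text shown names no primary outcome or time point and ties the sample size to no outcome

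*Protocol article*

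**What the plan says.** **Decision rule.** The Statistical analysis section gives one threshold for everything: "The results will be considered statistically significant if the P-value is less than 0.05". It states no multiplicity rule and no order among outcomes.

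**Outcomes and visits.** The same section lists social media use, child-family relationship, alcohol consumption and sexual health on an equal footing. The section on Phase 3 names five instruments: the Social Media Use Scale (SMUS), the Family Relationship Scales, the Family Leisure Activity Profile, AUDIT and the Sexual Health Practice Tool. They are given at baseline and "at four time points after implementation of the intervention", from T1 (right after the intervention) to T4 (three months later). No visit is singled out.

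**Methods.** GEE is introduced as the regression model, with its equations in S6 File (not shown). A repeated-measures ANOVA is then added to study effectiveness over the same periods.

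**Sample size.** The calculation for the intervention phase is made "for a 95% confidence level for the two-tailed hypothesis" and "to achieve a power of 90" per cent, "with an assumed standard deviation of population 0.15 and estimated effect size (D) of 5" per cent. It names no instrument, domain or visit to which that SD and effect belong.

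**Aims.** The abstract's Purpose includes reducing excessive social media use together with its adverse effects. The closing paragraph of the Introduction and the section Study aim and design list only alcohol, sexual health and child-family relationships as targets. The analysis section covers all four domains.

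**The concern.** A trial of effectiveness needs one question whose answer is fixed in advance. Under the stated rule, an effect could be claimed on whichever domain, visit or method falls below 0.05, and nothing in the text shown says which result decides. If social media use fell while alcohol use, sexual health and family outcomes did not change, the abstract's aim would suggest at least partial success. The aim in Study aim and design would suggest failure.

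The sample size cannot settle the matter, because it points to no outcome. The economic evaluation inherits the gap, since its cost-effectiveness ratio is expressed against study outcomes in general. The trial is also open-label, although data entry and analysis are to be masked, so a decision rule fixed before the results are seen is worth more than usual.

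**Working it through.** **1. Reproduce the plan's own figure.** Inputs from the sample size section for the intervention phase: Z = 1.96 and 1.2816, SD = 0.15, D = 0.05.

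n = 2(1.96 + 1.2816)² × 0.15² / 0.05² = 2 × 10.508 × 9 = 189.14

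This matches "a minimum sample size of 189 per arm/group is required for the study". With attrition, 189 × 1.10 = 207.9, or about 208. Then 208 × 2 = 416 per city and 416 × 3 = 1248, set to 1260. The whole 0.05 is spent on one comparison.

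**2. False-positive chance with independent tests.** For k correct 5% tests and no true effect anywhere, the chance of at least one significant result is 1 − 0.95^k.

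- k = 4 (one test per domain): 18.5%
- k = 5 (one test per instrument): 22.6%
- k = 16 (4 domains × 4 visits): 56.0%
- k = 20 (5 instruments × 4 visits): 64.2%

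**3. The same with correlated tests.** The documents give no correlations. The assumed values are 0 to 0.5 between outcomes and 0.5 to 0.9 between visits. Normal test statistics were simulated with 400,000 draws per setting, and the correlation across both outcome and visit was the product of the two.

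| Outcomes | Correlation between outcomes | One test each | 4 visits, corr. 0.5 | 4 visits, corr. 0.7 | 4 visits, corr. 0.9 |
|---|---|---|---|---|---|
| 4 | 0 | 18.5% | 49.1% | 42.8% | 32.5% |
| 4 | 0.5 | 15.6% | 42.6% | 36.6% | 27.3% |
| 5 | 0 | 22.7% | 57.2% | 50.1% | 38.8% |
| 5 | 0.5 | 18.4% | 48.5% | 41.9% | 31.6% |

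The range is therefore 16–23% for one test per outcome and 27–57% for 16 to 20 tests. The ANOVA would add somewhat to these figures. It uses the same data, so its results would be strongly correlated with the GEE's, and the addition has not been quantified.

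**4. What co-equal outcomes would cost.** Under Bonferroni, with the plan's formula, SD and D, per city:

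- 4 outcomes (alpha 0.0125): 258 per arm before attrition; 189 per arm gives 77% power.
- 5 outcomes (alpha 0.01): 268 per arm; 189 gives 75%.
- 20 tests (alpha 0.0025): 334 per arm; 189 gives 59%.

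These apply to 189 per arm in one city, which is how the plan sizes the trial. With the three cities pooled (3 × 189 = 567 per arm), the same formula gives 99.9% power for five outcomes. That formula has no term for clustering by school, so none of these powers should be taken as the trial's real power. They show only that 0.05 was budgeted for a single comparison.

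**The case against.** **Scope.** This is a condensed article. A multiplicity procedure is commonly left to the SAP, and Fig 1, S6 File and any SAP are not shown; one of them may name a primary outcome. This stands in part. The missing adjustment alone would be no finding, and all that can be said is that the text shown names no primary. But the article itself fixes a blanket threshold, gives a sample size attached to no outcome, and states aims that differ. Those are statements in the protocol, not details left for later.

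**Number of tests.** A reader might infer that 20 separate tests are planned, doubled by the second method, so that a false positive is likely. The documents do not support this. The Phase 3 section says when the tools are administered, not how many tests are run. The GEE may give one arm-by-time test per outcome or four visit contrasts. Only some settings with 16 to 20 separate, weakly correlated or independent tests pass 50%.

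**Ranking of methods.** GEE carries the adjustment and the formal specification, and the ANOVA is introduced as an addition. The natural reading is that GEE is the main analysis. That stands; the article only fails to say so outright.

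**Awareness.** A reader might also infer an unmeasured outcome from the Results chain section, where "The outcomes consist of reduction in time spent on social media, reduction in risky sexual behaviour, enhanced awareness regarding the risks of alcohol use" appears. That section describes a programme chain, and the tools are in S2 and S3 Files, which are not shown. Whether awareness items exist cannot be checked, and the question is separate from this one.

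**Conclusion.** The point holds in a limited form. The article applies one unadjusted 0.05 threshold to four co-equal domains. It names no primary outcome or visit in the text shown, leaves the deciding method implicit, and sizes the trial for a single comparison linked to no outcome. The abstract and the study aim differ on whether social media use is a target.

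If the intervention had no effect on anything, the chance of at least one false claim would be 16–23% or 27–57%, depending on whether each outcome gets one longitudinal test or a test at each visit. With 20 independent tests it would be 64%. Every scenario is at least three times the nominal 5%. The figures rest on the assumed correlations, the assumed number of tests, and each test being a correct 5% test. They do not show that a false positive is more likely than not, nor that no success criterion exists in documents not shown.

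**What to change.** Before outcome data are analysed:

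1. In Statistical analysis, name one primary outcome and one primary time point, or one overall arm effect across T1 to T4. State that the GEE arm contrast at two-sided 0.05 decides and that the ANOVA is supportive only.
2. In the sample size section for the intervention phase, say which outcome the SD of 0.15 and the 5% effect refer to, and check that they suit it.
3. Bring the abstract's Purpose, the Introduction, Study aim and design, and Statistical analysis into line with that choice.
4. Treat the remaining outcomes as secondary, either tested with Holm adjustment or reported as estimates with 95% intervals.

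The choice belongs to the sponsor. SMUS at T1 is one option that fits the abstract. It fits less well with Study aim and design, which does not list social media use as a target; making it a gatekeeper could leave every outcome in that section without a formal test. If a document not shown already names the primary, it is enough to state it in these sections.

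The error rate for the primary claim would then be 5%, and the plan's formula would still give 90% power with 189 per arm on its own assumptions. The change is a short paragraph and needs no new data or participants. Data collection is planned to run to 30/06/2027, so it can still be made before analysis. The downside is that fewer secondary results can be called significant.

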### Economic evaluation

For the economic evaluation of the developed intervention, both the costs and consequences (health outcomes) will be assessed using WHO’s CHOICE frameworks (Fig 4). The following costs and health outcomes shall be assessed:

**Fig 4 pone.0354663.g004:**
[figure not shown]
Economic evaluation of SM intervention.

*Costs of the social marketing intervention*- The total cost in each scenario will be calculated from a societal perspective. The Intervention cost shall include programmatic costs (direct and indirect costs). The manpower costs shall be apportioned and annualized. It shall also include administrative costs, travel costs, quality assurance and monitoring, follow-up screening results, and logistics costs, etc. Thus, five-year costs for both intervention and comparator will be modelled using a hybrid economic evaluation simulation model.*Comparator*- The intervention will be compared to the hypothetical “null” scenario in which the effects of the currently implemented intervention will be removed.

A hybrid economic evaluation simulation model is proposed for this evaluation of the social marketing intervention developed under the study. The actual model will depend on the final study outcomes and parameters available. The data will be entered in Microsoft Excel 2019, and models will be built using TreeAge Pro.

The transition probabilities from the literature will be employed for the parameters within the model. Both costs and outcomes will be discounted at 3% annually, in line with international standards and prior Indian evaluations [19].

Cost-effectiveness analysis shall be undertaken. The endpoint for the CEA will be the Incremental Cost-Effectiveness Ratio. Cost-effectiveness is defined as the ratio of incremental costs to incremental outcomes. The incremental cost will be the difference between the total expected cost of the intervention and the total expected cost of no intervention [19]. The performance of interventions evaluated by this model will be measured using the cost-effectiveness ratio.

The following formula will be used for this computation:

$$\begin{array}{c} \text{ICER }=\;(\text{C2}-\text{C1})/(\text{E2}-\text{E1}) \end{array}$$

The numerator in the above equation implies the incremental costs, while the denominator implies the incremental effects. Here, C2 and C1 are the costs of intervention and comparator, respectively, while E2 and E1 are the effects of intervention and comparator, respectively. The incremental cost-effectiveness ratio per unit change in study outcomes will be calculated. A threshold between 1 and 3 times of GDP-Gross Domestic Product (as per WHO guidelines) may be used to consider the cost-effectiveness of the intervention, so as to consider for routine implementation as part of the national programme.

Both univariate and probabilistic sensitivity analysis will be conducted. Results from uncertainty analysis will be presented as a cost-effectiveness plane as well as a cost-effectiveness acceptability curve.

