#### Delivering the intervention.

A novel Social Marketing Intervention (SMI) will be provided for three months, once per month. The duration of each session will be between 1 hour and 1.5 hours. Social marketing is the application of marketing techniques and strategies to the analysis, planning, execution, and evaluation of programs designed to influence the voluntary behaviour of target audiences to improve their health outcomes, personal welfare, and that of their society [18]. The control group shall receive basic counselling consisting of awareness aimed at limiting social media use. An early version of the intervention is attached in the S5 File.

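### The ICER is expressed per unit of study outcome but may be judged against a GDP threshold, with no conversion to a common health unit stated

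*Protocol article*

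**What the plan says.** All of this is in the protocol article.

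- **Unit of the ratio** (Economic evaluation): "The incremental cost-effectiveness ratio per unit change in study outcomes will be calculated".
- **Decision rule** (same section, next sentence): "A threshold between 1 and 3 times of GDP-Gross Domestic Product (as per WHO guidelines) may be used to consider the cost-effectiveness" of the intervention, with a view to adopting it in the national programme.
- **Study outcomes** (Statistical analysis): "social media use and its attributable child-family relationship, alcohol consumption, as well as sexual health issues". The same section says that some are continuous and some categorical.
- **Comparator** (Economic evaluation): a hypothetical null "scenario in which the effects of the currently implemented intervention will be removed". Incremental cost is "the difference between the total expected cost of the intervention and the total expected cost of no intervention". In the ICER formula, "E2 and E1 are the effects of intervention and comparator, respectively", and C2 and C1 are defined in the same way for cost.
- **Control arm of the trial** (Delivering the intervention): "The control group shall receive basic counselling consisting of awareness aimed at limiting social media use".
- **Model** (Economic evaluation): a five-year simulation model within a named WHO framework, with transition probabilities from the literature and discounting of costs and outcomes. Its final form is left to depend on the outcomes and parameters available. A cost-effectiveness plane, an acceptability curve, and univariate and probabilistic sensitivity analyses are planned.

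**The concern.** A cost-effectiveness threshold is a price for one unit of effect. It can judge a ratio only if that ratio is in the same unit. Here the ratio is money per point, or per category change, on measures of social media use, family relationship, alcohol and sexual health. The threshold is a multiple of GDP with no effect unit attached. A GDP multiple does not value a point on a family-relationship scale, and a point on one instrument is not comparable with a point on another.

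The Introduction presents the economic evaluation as evidence for sustainability and scale-up within an existing national school health programme. The threshold is where that evidence would become a yes or no, and as written the answer would depend on how the questionnaires are scored.

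The second issue is the link between model and trial. The trial randomises the social marketing intervention against counselling that itself aims to limit social media use. The economic section compares the intervention with nothing and never uses the counselling arm. The one contrast protected by randomisation therefore has no stated ICER, and the effect against the null must come from somewhere the text does not describe.

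**Working it through.** The protocol states no ICER, cost or threshold amount, so there is no figure to reproduce. The check sets the definitions side by side and then illustrates what follows from them.

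**1. Dependence on scale**

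Inputs:
- ICER = (C2 − C1)/(E2 − E1), from Economic evaluation.
- Incremental cost per student C, left as a symbol.
- Effect of 5%, the value D in Sample size for the intervention phase. Reading it as 0.05 on a 0–1 scale is an assumption.
- Scale ranges 0–1, 0–40 and 0–100, assumed for illustration.

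If the scale runs from 0 to s, the same relative effect is 0.05 × s points, so ICER = C/(0.05 × s).

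| Scale | Effect in points | ICER per point |
|---|---|---|
| 0–1 | 0.05 | C/0.05 = 20 × C |
| 0–40 | 2 | C/2 = 0.5 × C |
| 0–100 | 5 | C/5 = 0.2 × C |

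The spread is 20/0.2 = 100-fold with nothing changed in the students or the costs. In general, multiplying a scale by ten divides its ICER by ten.

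Let the threshold be T. The intervention passes on the 0–1 scoring if 20 × C < T, that is C < 0.05 × T. It passes on the 0–100 scoring if 0.2 × C < T, that is C < 5 × T. For any incremental cost per student between 0.05 × T and 5 × T, the verdict is decided by the scoring alone.

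**2. Several outcomes, one threshold**

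Statistical analysis lists four outcome domains, so one ICER per study outcome means at least four ratios in different units. A single T cannot be the value of one unit of each.

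**3. Is a common unit stated elsewhere?**

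The economic text names no DALY, QALY or other generic unit, and no mapping from the instruments to one. DALYs appear only as background in the Introduction.

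**4. Comparator**

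| Source | Contrast |
|---|---|
| Economic evaluation, cost and effect | Intervention against the null |
| Randomised trial, effect | Intervention against basic counselling |

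The two ICERs answer different questions. Suppose that counselling achieves a share f of the intervention's effect against the null, and costs a share g of the intervention. Then ICER against counselling ÷ ICER against null = (1 − g)/(1 − f). Assumed values from 0 to 0.5:

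- f = 0, g = 0.5: 0.5/1 = 0.50
- f = g: 1.00
- f = 0.5, g = 0: 1/0.5 = 2.00

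The gap can go either way. The trial cannot estimate f, because no arm goes without both counselling and the intervention.

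**The case against.** **The threshold is optional, and a unit may be given elsewhere.** The text says that the threshold may be used, not that it will be. It promises health outcomes and points to Fig 4, which is not available here. A five-year model with discounted outcomes could well produce a generic health outcome. This stands against any claim that the verdict would necessarily be invalid. It does not remove the mismatch: the sentence that fixes the ratio per unit of study outcome is followed directly by the GDP threshold, and a unit named in the figure would then conflict with that sentence.

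**The comparator is a declared choice.** A reader might infer that the plan puts a cost against no intervention over a trial effect against counselling, and so mixes two comparators in one ratio. The text does not say this. C1 and E1 are both defined for the same comparator, the null, and nowhere is the trial contrast named as E2 − E1. A null comparator is also a legitimate modelling choice under the named framework, and literature parameters could link the trial effect to it. An article may leave such model detail to a fuller document. All of this stands. What remains is narrower: the randomised contrast is not reported in economic terms, and no link from counselling to the null is described.

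**Part of the remedy is already planned.** The acceptability curve needs no single threshold. This is true, and it makes the correction cheap.

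**Conclusion.** The unit mismatch holds and carries the point. An ICER per unit of a study outcome cannot be read against a multiple of GDP unless the outcome is first converted to a common health unit, and the text states no conversion. Rescaling an outcome tenfold moves its ICER tenfold against the same threshold. The 100-fold illustration rests on an assumed effect of 5% of the scale range and assumed ranges of 0–1 and 0–100, but the dependence on scale does not rest on those values.

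The comparator point is secondary. The null is not wrong in itself, and the documents do not show two comparators combined in one ratio. The gap is that the only randomised effect, against counselling, has no stated place in the economic analysis. The 0.50 to 2.00 range is illustrative and depends on the assumed shares f and g.

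The proper conclusion is that the threshold comparison is not interpretable without a conversion. The stronger inference, that the cost-effectiveness verdict will be invalid, is not supported, because the threshold is optional, the model is still open and Fig 4 is not shown. The economic evaluation is an additional aim, so the trial's effectiveness analysis is unaffected.

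**What to change.** In Economic evaluation:

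1. State that the GDP-based threshold, worded per capita, applies only to an ICER per generic health unit, such as a DALY or QALY, derived in the planned model. Name the unit and say how the study outcomes map to it.
2. For each ICER per unit of a study outcome, drop the threshold. Report the planned acceptability curve over a range of willingness to pay, with the scoring of the scale given.
3. Add the ICER for the randomised contrast, with C1 and E1 taken from the basic-counselling arm.
4. Keep the null as a labelled scenario, with its assumed effect and source, so that cost and effect always share a comparator.

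Items 1, 2 and 4 are mainly wording, plus the mapping work if a DALY or QALY ratio is wanted. Item 3 needs the counselling arm to be costed while the trial runs; data collection is planned to end on 30/06/2027. The downside is a little more costing work and possibly no single yes/no verdict for the scale outcomes.
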